## Abstract

**Background:**

Low back pain is a common symptom and continuous or recurrent pain results in chronic low back pain (CLBP). While many patients with CLBP have tried various treatments, complementary and alternative medicine including acupuncture and herbal medicine is one of the commonly used treatments. Palmijihwang-hwan is a herbal medicine used frequently in clinical practice but there has been no report of the efficacy, safety, or cost-effectiveness analysis of Palmijihwang-hwan for CLBP.

**Methods:**

This study is a randomized, assessor-blinded, multicenter, clinical trial with two parallel groups. Four Korean medicine hospitals will recruit 84 participants and randomly allocate them into the control or treatment group in a 1:1 ratio. The control group will receive acupuncture treatment at 11 local and 4 distal acupuncture points for 20 min twice a week for 6 weeks. The treatment group will receive the same acupuncture treatment as the control group and also take Palmijihwang-hwan for 6 weeks. The primary outcome will be the change in visual analog scale (VAS) score between baseline (visit 1) and completion of the intervention (visit 12), and secondary outcomes will be pain-related clinical relevance (minimal clinical important difference or the proportion of the participants who decrease more than 30, or 50% on VAS), disability (Roland and Morris Disability Questionnaire), quality of life (EuroQol-5D), global assessment (Patient Global Impression of Change), and economic analysis (cost-effectiveness and cost-utility analysis). Additionally, safety will be assessed.

**Discussion:**

The results of our study will provide the clinical evidence about the efficacy, safety, and cost-effectiveness analysis of Palmijihwang-hwan for CLBP. There will be a chance to provide multiple subdivided influence of this treatment with various outcome measures, but lack of placebo is our limitation.

**Trial registration:**

Clinical Research Information Service, KCT0002998. Registered on 12 July 2018.

## Background

Low back pain (LBP) is a symptom that 84% of humans experience at some time in their life [1]. LBP can be classified according to its duration into acute (< 6 weeks), subacute (6–12 weeks), and chronic (> 12 weeks) [2]. Most patients with acute LBP recover within 4 weeks but recurrences are common [3]. In the case of insufficient treatment and management, continuous pain results in chronic LBP (CLBP), which is known to be related to various factors including psychological distress and psychiatric disorders [4]. Deficits in and poor satisfaction with conventional treatments [5] for CLBP have led to attempts to treat CLBP using nonpharmacologic [6] or complementary and alternative medicine (CAM).

In Korean medicine, several treatments including acupuncture [7], electroacupuncture [8], and pharmacopuncture such as bee venom [9] have been examined as a treatment for LBP, and several studies have reported therapeutic effects. Particularly, acupuncture is a well-known treatment for CLBP. Various studies have reported on the effects on pain [10] and the pragmatic aspects [11] of acupuncture in treating CLBP and some have suggested that acupuncture has more effect on the reduction of pain and bothersomeness than sham control in patients with CLBP [12]. Several studies have investigated the clinical effect of acupuncture combined with other treatments such as direct moxibustion [13], physiotherapy [14], and pharmacopuncture [15]. However, studies on the effects of adjuvant Korean herbal medicines on CLBP, particularly in combination with acupuncture, are rare.

Among them, Palmijihwang-hwan (Ba-Wei-Di-Huang-Wan in Chinese and Hachimi-jio-gan in Japanese) has been reported to be useful for skeletal muscle proliferation [16] and to be helpful for patients with sciatic neuralgia or lumbago with bad circulation in the lower body [17], which is similar to the symptoms of CLBP. Eight herbs used in Palmijihwang-hwan are also reported to have analgesic effects in experimental studies. It is reported that *Aconitum carmichaelii* improves inflammatory conditions by mediating TNF-alpha response [18] and processed *A. carmichaelii* exerts an analgesic effect via central opioid receptors [19]. Catapol, an ingredient in *Rehmannia glutinosa*, alleviates neuropathic pain with the modulation of neuroinflammation in the spinal cord in rats [20]. *Cornus officinalis* is reported to have anti-inflammatory and analgesic effects [21], while *Dioscorea batatas* is confirmed to have anti-inflammatory activity through the inhibition of iNOS and COX-2 expression [22]. Scientific studies indicate the anti-inflammatory effects of *Alisma orientale* [23]*, Poria coccos* [24]*, Paeonia sulffruticosa* [25]*, and Cinnamomum cassia* [26].

However, these reports include no clinical study to confirm the efficacy or safety of Palmijihwang-hwan or to include a cost-effectiveness analysis (CEA) of Palmijihwang-hwan, for treatment of CLBP. Therefore, we describe a protocol for a randomized controlled clinical trial that uses Palmijihwang-hwan combined with acupuncture for treatment of CLBP.

## Methods and design

### Objectives

The purpose of this study is to investigate the efficacy, safety, and CEA of Palmijihwang-hwan combined with acupuncture for treatment of CLBP by comparing this with the effects of acupuncture treatment alone.

### Design

This study is a randomized, assessor-blinded, multicenter, clinical trial with two parallel groups. We intend to investigate the synergic effects of Palmijihwang-hwan with acupuncture treatment in patients with CLBP. Eligible participants will be assigned to one of two groups, the control group (only acupuncture) or the treatment group (Palmijihwang-hwan + acupuncture). The flowchart is as shown in Fig. 1. The Standard Protocol Items: Recommendations for Interventional Trials (SPIRIT) checklist is provided in Additional file 1.

**Fig. 1 Fig1:**
[figure not shown]
Study flowchart

### Sample size calculation

We performed sample size calculations to determine the appropriate number of participants. The purpose of this study is to verify the synergic effect of the combination treatment (acupuncture + Palmijihwang-hwan) compared to acupuncture treatment alone, using a visual analog scale (VAS) score for change between baseline and completion of the intervention (6 weeks). However, no study has been conducted to investigate the effects of Palmijihwang-hwan combined with acupuncture in the treatment of CLBP. Thus, we reviewed a similar study conducted in patients with CLBP [27] in which the authors evaluated the efficacy of a herbal formula, Ojeok-san, by measuring the VAS score change between baseline and completion of the intervention (4 weeks) and comparing this with the placebo group in randomized clinical trials of CLBP. In that study, the change in VAS score between baseline and completion of the intervention was − 26.41 ± 19.06 in the treatment group and − 12.83 ± 19.45 in the control group. Based on these data, 33 participants would be required per intervention group for a two-arm study and a two-tailed test with 0.80 power (1-β) at the 0.05 α level, as calculated using G* Power (Version 3.1.9.3) [28]. After assuming a 20% drop out rate, we calculated that we would need to recruit 42 participants per group. Thus, a total of 84 participants will be required.

### Participants

We will recruit 84 participants with CLBP and assign them randomly to the control group or the treatment group in a 1:1 ratio.

#### Inclusion criteria

#### The inclusion criteria are:

Patients with CLBP, aged 19–65 yearsChief complaint of LBP lasting > 3 monthsScore > 4 cm on a 10-cm VAS for LBP at one week prior to enrollmentVoluntarily agreeing to participation and observance of trials with written consent

#### Exclusion criteria

#### The exclusion criteria are:

Hypersensitive reactions to or history of reactions to Palmijihwang-hwan or its componentsAbnormalities in the lower extremity on neurological examinationRequirement for surgical treatment because of severe neurological deficits (sensory or motor) or cauda equina syndromePrevious spinal surgery or scheduled spinal surgery during the trialPatients with scoliosis or neurodegenerative diseaseVertebral fracture, inflammatory spondylitis, spinal infection, or malignant tumorPregnancy, lactation, plans to conceive, refusal to use appropriate contraception methods during the trialGastrointestinal disorders or diarrheaGenetic disorders such as galactose intolerance, Lapp lactase deficiency, or glucose-galactose malabsorptionUse of acupuncture, herbal medicine, injection, physical therapy, or manipulation treatment for low back pain within two weeksChief complaint of part other than the lumbar regionParticipants in other clinical studies related to CLBP within a monthIneligibility for the trial as judged by the investigator

### Recruitment

Four Korean medicine hospitals, Kyung Hee University Korean Medicine Hospital, Kyung Hee University Korean Medicine Hospital at Gangdong, Oriental Medicine Hospital of Daegu Haany University, and Dongguk University Bundang Oriental Hospital, will recruit participants through advertisements on bulletin boards, local newspapers, and public boards.

### Procedure

The study schedule is as shown in Fig. 2. At the screening visit, patients who are interested in participation and who visit one of the four Korean medicine hospitals will be informed about the study. They will be also informed about expected benefits and risks and that they are able to withdraw from the study at any visit. If they sign the informed consent form voluntarily, the investigator will perform several examinations including check of vital signs, physical examination, spine x-ray, blood chemistry test, pregnancy test, and will collect demographic data, CLBP history, and concomitant treatment data, and apply the VAS, to determine the patient’s eligibility. If patients are eligible for the study but are taking medication, the investigator will determine the day of screening according to the participant’s medication to give a washout period. If the participant is taking anti-inflammatory medication or painkillers, the investigator will give a 2-week washout period. During the 6-week treatment, the participants in both groups will visit the hospital twice a week (total 12 visits) and receive acupuncture treatment at every visit. Participants in the treatment group will additionally receive Palmijihwang-hwan (at visit 1, 4, and 8) during the treatment period. Then, participants in both groups will be asked to complete a survey every 2 weeks (at visit 4, 8, and 12). On visit 13, 4 weeks after visit 12, all participants will visit the hospital for the final time.

**Fig. 2 Fig2:**
[figure not shown]
Study schedule (Standard Protocol Items: Recommendations for Interventional Trials, SPIRIT). Abbreviations: EQ-5D: EuroQol-5 dimension; PGIC: patient global impression of change; RMDQ: Roland and Morris disability questionnaire; VAS: visual analog scale

### Randomization and allocation concealment

A randomization sequence will be generated by an independent statistician who does not participate in this study, using R software (Version 3.5.0; R Foundation for Statistical Computing, Vienna, Austria). Randomization will be stratified based on four Korean medicine hospitals, and then block randomization will be used to approximately equalize the number of participants in each group. A random code will be delivered in the sealed envelopes, in which the allocated group is written. A delegated investigator in each site will open the envelope in sequence and allocate a participant to either intervention or control arm, only when all the screening criteria are satisfied. Allocation will be concealed until the investigator opens each sealed envelope. The randomization sequence will be kept by the independent statistician or physician during the clinical trial period and concealed until the occurrence of the event predefined as a reason for code-breaking.

### Blinding

The additional Palmijihwang-hwan treatment means that the participants and practitioners cannot be blinded; thus, the practitioners who perform the acupuncture treatment or provide Palmijihwang-hwan will not assess the outcome. The assessor who record case report form (CRF) will be instructed to ask questions simply and write in detail the participant's answer. Both of the assessor and participant are prevented from talking about the treatment.

### Interventions

#### Control group intervention

Participants in the control group will receive only the acupuncture treatment. Sterilized stainless steel needles with 0.25 mm width and 40 mm length (DB108C; Dongbang Medical Co., Boryung-si, South Korea) will be inserted at 11 local and 4 distal acupuncture points for 20 min. Acupuncture points are as shown in Table 1. Participants will receive the acupuncture treatment twice a week for 6 weeks, performed by Korean medical doctors who are specialists in acupuncture and moxibustion.

**Table 1 Tab1:** Acupuncture treatment protocol based on the Standards for Reporting Interventions in Clinical Trials of Acupuncture (STRICTA) [29]

1. Acupuncture rationale	1a) Acupuncture technique	Traditional Korean medicine theory
	1b) Reasoning for treatment provided (based on historical context, literature sources, and/or consensus methods), with where appropriate	Textbook of acupuncture and moxibustion and related articles
	1c) Extent of treatment variations	EX-B2 of lesion or upper and lower levels
2. Details of needling	2a) Number of needle insertions per subject per session	Acupuncture points: 15
	2b) Names of points used	Local acupuncture points: GV3, EX-B5/bilateral BL23, BL24, BL25, BL26 (total 11 points) Distal acupuncture points: bilateral BL40, BL60 (total 4 points)
	2c) Depth of insertion based on a specified unit of measurement	20–40 mm
	2d) Response sought	De-qi (penetrating, sharp, aching and painful sensations)
	2e) Needle stimulation	Rotation of the acupuncture needle 3–5 times
	2f) Needle retention time	20 min
	2 g) Needle type	Sterilized stainless steel needle with 0.25 mm width and 40 mm length (DB108C; Dongbang Medical Co., Boryung-si, South Korea)
3. Treatment regimen	3a) Number of treatment sessions	12 sessions
	3b) Frequency and duration of treatment sessions	Twice a week for six weeks (Total 12 times)
4. Other components of treatment	4a) Details of other interventions used for the treatment group	Lifestyle advice about chronic low back pain
	4b) Setting and context of treatment, including instructions to practitioners and information and explanations for patients	Practitioners are instructed to prevent talking with participants
5. Practitioner background	5) Description of participating acupuncturists	Korean medical doctors who are specialist in acupuncture and moxibustion at least three years of experience, or under supervision by a specialist
6. Control interventions	6a) Rationale for the control or comparator in the context of the research question with sources that justify this choice	Textbook of acupuncture and moxibustion and related articles
	6b) Precise description of the control or comparator	Same acupuncture treatment in two groups: not applicable
	If sham acupuncture or any other type of acupuncture-like control is used, provide details as for items 1–3.	Same acupuncture treatment in two groups

#### Treatment group intervention

Participants in the treatment group will receive the same acupuncture treatment as the control group and will also take Palmijihwang-hwan. At visit 1, 4, and 8, they will receive 2-week doses of Palmijihwang-hwan (14 days + an extra 7 days) in an individual package from the practitioners. The Palmijihwang-hwan that will be used in this study is a brown, bitter herbal extract granule produced and packed by Kracie Pharma Korea Co., Ltd. (Seoul, Korea) in accordance with the Korean Good Manufacturing Practice guidelines. Palmijihwang-hwan contains eight herbs (listed in Table 2), is water-extracted with starch and lactose, and is regulated by the Korean Food & Drug Administration. At the production stage, each herb is tested for properties, morphology, and undergoes physicochemical and microorganism examination. Then Palmijihwang-hwan is produced by extraction, separation, concentration, drying, and granulation with compound herbs. Multiple quality tests are performed, including pattern analysis of the ingredients contained to ensure quality and stability, and we will test for residual pesticides to ensure product safety. Palmijihwang-hwan, packed for one dose, will be provided by an independent pharmacist in a separate room and participants will be instructed to take it with water 30 min after breakfast and after dinner, for 6 weeks.

**Table 2 Tab2:** Ingredients of Palmijihwang-hwan

Scientific name	Proportion
*Rehmannia glutinosa (steamed 9 times)*	5.0
*Cornus officinalis*	3.0
*Dioscorea batatas*	3.0
*Alisma orientale*	3.0
*Poria coccos*	3.0
*Paeonia sulffruticosa*	3.0
*Cinnamomum cassia*	1.0
*Aconitum carmichaelii (processed)*	1.0

#### Concomitant treatment

Other interventions including muscle relaxants, non-steroidal anti-inflammatory drugs (NSAIDs) (oral medication, topical application, or patch), antidepressant agents, anticonvulsants, treatments with Korean medicine (acupuncture, herbal medicine, and cupping), physical therapy, injections, or surgery will not be permitted during the treatment period (but are permitted during the follow-up period). However, concomitant medications taken within 4 weeks before trial participation or that are considered to have no effect on the interpretation of the results of this study may be allowed dependent on the judgment of the investigator.

#### Adverse events

Adverse events will be checked at every visit. If adverse events occur, the practitioners will record them in detail in the CRF and decide upon trial continuation depending on the symptoms. Abnormal change in blood chemistry tests, vital signs, or change of medication/treatment will also be checked.

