### Withdrawal criteria

### The withdrawal criteria are:

Violation of the inclusion criteria or applicable to exclusion criteriaSerious adverse events that make it difficult to maintain the trialRefusal to continue, withdrawal of consent by the participants and/or legal representativeCompliance with Palmijihwang-hwan or acupuncture treatment less than 80% (participants should take more than 23 of the total 28 doses of Palmijihwang-hwan given at the time of the visit and receive more than 10 of the total 12 acupuncture treatments)Violation of the clinical trial protocol by the investigator or the participantsLoss to follow upUse of medications or treatments that affect the results of the trials without the permission from the practitionerInappropriate process as judged by the investigator

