### Statistical analysis

Continuous variables at baseline will be expressed as means plus/minus standard deviation and statistically tested using the two-sample *t* test or the Wilcoxon rank sum test. Categorical variables at baseline will be expressed as frequencies and statistically tested using the chi-squared test or Fisher’s exact test. If there is a significant difference between groups, the baseline variable will be considered as a covariate for efficacy analysis.

The full analysis set (FAS) will be analyzed primarily, including participants who take at least one dose of Palmijihwang-hwan and complete at least one pain assessment. Also, the per-protocol set (PPS) will be subordinately analyzed, including participants who take more than 80% of the total Palmijihwang-hwan dose and complete the trial. In the FAS analysis, the missing data will be imputed using the method of last observation carried forward. The primary outcome (change in the VAS score between baseline and endpoint) will be tested by analysis of covariance (ANCOVA) or rank ANCOVA (according to normality or homoscedasticity) with factors of group and study site and covariates of baseline values. Continuous variables for the secondary outcomes will also be tested, respectively, by ANCOVA or rank ANCOVA. Categorical variables for the secondary outcomes will be tested by chi-squared test or Fisher’s exact test according to the number of the cells with a value of 5 or less in the contingency table. Every variable predefined in the outcome sections will be compared at each time point, respectively.

The safety set will include participants who receive at least one dose of Palmijihwang-hwan. In safety analysis, the frequency and ratio of adverse events will be applied and compared between the treatment group and the control group using the chi-squared test or Fisher’s exact test. Any abnormal change in blood chemistry tests from visit 1 to 12 will be expressed as frequency and percentage and compared between the treatment group and the control group using McNemar’s chi-squared test, and any change in vital signs between visit 1 and 12 and between visit 1 and 13 will be expressed as change scores and compared between the treatment group and the control group using the two-sample *t* test or the Wilcoxon rank-sum test. Statistical tests will be carried out at 5% significance level (two-sided), using R software (Version 3.5.0 or later; R Foundation for Statistical Computing, Vienna, Austria).

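### Low herb compliance, and adverse events at the practitioner's discretion, can end trial participation rather than only treatment, and LOCF then supplies the week-6 VAS; the herb-dose item can remove only treatment-group participants

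*Protocol article*

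**What the plan says.** Under Withdrawal criteria, the Protocol article lists compliance below 80% with the herb or with acupuncture alongside withdrawn consent and loss to follow-up. A bracket spells out the herb part as "participants should take more than 23 of the total 28 doses of Palmijihwang-hwan given at the time of the visit" and the acupuncture part as "receive more than 10 of the total 12 acupuncture treatments". The same list has an item for serious adverse events that stand in the way of continuing.

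Under Adverse events, when an event occurs, the practitioners document it and "decide upon trial continuation depending on the symptoms". What is being decided is staying in the trial, not staying on treatment. The Blinding section states: "The additional Palmijihwang-hwan treatment means that the participants and practitioners cannot be blinded".

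Treatment-group participants are told to "take it with water 30 min after breakfast and after dinner, for 6 weeks", which is two doses a day. For the other arm, the article says: "Participants in the control group will receive only the acupuncture treatment".

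Under Statistical analysis, the full analysis set (FAS) is primary. "In the FAS analysis, the missing data will be imputed using the method of last observation carried forward". The per-protocol set (PPS) already requires more than 80% of the herb dose and completion of the trial. The primary outcome is the VAS change from visit 1 to visit 12. The Procedure section places surveys at visits 4, 8 and 12, and a final visit 13 four weeks later.

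**The concern.** Stopping a treatment and leaving a trial are different events, and the withdrawal list does not separate them. Someone who misses several days of granules could still report pain at week 6, and that value is the primary outcome. If the participant is instead taken out of the trial, an older VAS stands in for week 6.

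The herb-dose item has no counterpart in the control group. The acupuncture item and the adverse-event wording apply to both arms. If the herb-dose item produces extra exits in one arm, the LOCF error does not cancel in the comparison. Carrying an early value forward understates improvement where pain would have kept falling. Carrying a late value forward can preserve relief that was lost after the herb was stopped. Withdrawal is not needed to deal with adherence, because the PPS already does so.

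**Working it through.** **1. The plan's own figures.** From Sample size calculation: changes of -26.41 (SD 19.06) and -12.83 (SD 19.45), read here as mm on a 100-mm scale.

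- Planned difference: 26.41 - 12.83 = 13.58 mm.
- Pooled SD: sqrt((19.06² + 19.45²)/2) = 19.256, so the standardised difference is 13.58/19.256 = 0.705.
- A two-sided t-test at 5% with 80% power needs 32.55, so 33 per group. Then 33/0.80 = 41.25, so 42 per group and 84 in total. The stated sample size reproduces and is not in dispute.

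**2. When the dose item is triggered.** A two-week supply counts 28 doses (2 a day for 14 days).

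- 80% of 28 = 22.4.
- 22 taken (6 missed, about 3 days): 22/28 = 78.6%, below 80%.
- 23 taken (5 missed): 23/28 = 82.1%. This meets the 80% criterion but fails the bracketed count.

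So 6 missed doses meet the stated criterion; the bracket, read literally, makes it 5.

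**3. Which VAS is carried forward.** Supplies are handed out at visits 1, 4 and 8, so a per-supply count most naturally falls at visits 4, 8 and 12, which are also the survey visits. A compliance withdrawal would then have the week-2 or week-4 VAS in hand. A shortfall found only at visit 12 need not lose the primary value. Baseline would be carried forward only for an adverse-event exit before visit 4.

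**4. Illustrative size for compliance withdrawals.** The article does not give the following, so they are assumed:

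- x = 2, 4 or 6 more stops in the herb group than in control (5%, 10% or 14% of 42);
- linear improvement to the planned week-6 change;
- a true week-6 improvement after stopping between 12.83 mm (herb benefit lost) and 26.41 mm (kept).

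LOCF improvement: 26.41/3 = 8.80 mm from week 2, and 2 × 26.41/3 = 17.61 mm from week 4.

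Shift in estimated benefit = (x/42) × (LOCF improvement - true week-6 improvement). A negative value understates the herb. The bracketed differences are:

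- week 2, kept: 8.80 - 26.41 = -17.61
- week 2, lost: 8.80 - 12.83 = -4.03
- week 4, kept: 17.61 - 26.41 = -8.80
- week 4, lost: 17.61 - 12.83 = +4.78

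Shift in mm, from unrounded values:

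| Excess stops | Week 2, kept | Week 2, lost | Week 4, kept | Week 4, lost |
|---|---|---|---|---|
| 2 | -0.84 | -0.19 | -0.42 | +0.23 |
| 4 | -1.68 | -0.38 | -0.84 | +0.45 |
| 6 | -2.52 | -0.58 | -1.26 | +0.68 |

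Divided by 13.58 mm, the outer columns give -6% to +2%, -12% to +3% and -19% to +5%. Only the excess stops are counted; stops equally frequent in both arms are left out.

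**The case against.** The strongest objection is that the article never says outcome collection ends at withdrawal. It condenses a fuller protocol (version 2.1) that is not shown, and that document may provide a visit after early discontinuation. If withdrawn participants are still seen at visit 12, LOCF has nothing to fill. This stands as a limit: the loss of the visit-12 VAS is the natural reading of a withdrawal list and of a decision about staying in the trial, but it is an inference. It does not remove the point, because making low compliance a ground for withdrawal is a stated rule, not an omission.

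The arm difference is also assumed. There are no event or stop rates, controls face the acupuncture and adverse-event rules too, and 20% dropout is already allowed for. That is correct. The dose item creates the possibility of an imbalance; it does not establish one.

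Three stronger readings are tempting, and the document does not support them.

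- **Any adverse event ends participation.** The Adverse events section gives the practitioner discretion, and the only adverse-event item in the withdrawal list is limited to serious events. The two places do not contradict each other.
- **A 2.5-day pause is enough.** Five missed doses fail only the bracketed count. The criterion itself is below 80%, and 23 and 10 are the smallest whole numbers that reach 80% of 28 and of 12, so the bracket may well have been meant as at least.
- **LOCF carries baseline pain forward for people removed for missed doses.** That needs an exit before visit 4, which does not fit a count made per supply. Such a person might not be in the FAS at all, if the one required pain assessment means one after baseline.

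**Conclusion.** The point holds as a cheap improvement, not as a flaw that undermines the trial. The herb half of the compliance item is a stated reason to leave the trial that can apply to one arm only, and the primary analysis then substitutes an older VAS for week 6.

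Under the assumptions shown, six excess withdrawals shift the estimate by at most about 2.5 mm against the herb or 0.7 mm in its favour; two shift it by less than 1 mm either way. A reader might infer a bias in a known direction. The calculation does not support that: the sign depends on when people stop and on whether the benefit lasts, and the article says nothing on either. The conclusion also rests on the inference that no visit-12 VAS is collected after withdrawal. The sample size is unaffected.

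**What to change.** - **Withdrawal criteria:** split the list. Low compliance and adverse events become reasons to stop study treatment only. Withdrawal of consent and loss to follow-up remain reasons to leave the trial.
- **Adverse events:** let the practitioner decide whether study treatment continues, not whether the participant stays in the trial.
- **Follow-up:** ask participants who stop treatment for VAS and adverse events at visits 12 and 13, unless they withdraw consent.
- **Statistical analysis:** use these observed values in the FAS in place of LOCF.

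The visits are already scheduled and the total stays at 84. The cost is an ethics amendment and brief retraining at four sites. Some participants who stop will still decline to return, so some values will remain missing.
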